### Overview of design

2.1

This is a randomized waitlist-controlled trial, registered prior to participant recruitment at https://www.clinicaltrials.gov (NCT06028334). As shown in Figure 1, after a baseline assessment, participants are randomized 1:1 into IT (10 weeks of GetUp&Go intervention) or WL (10 weeks on waitlist), after which the primary outcome is measured. WL participants then receive 10 weeks of GetUp&Go. The 10-week treatment period (for all participants) is termed the Acquisition or A phase. Directly after the A phase, participants are re-randomized 1:1 into the Follow-Through (FT) phase: 10 additional weeks, of either RB or No Tx. A final outcome assessment and a debriefing interview are conducted at the end of the FT phase.

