Adverse events (AEs) are documented systematically throughout the trial. AEs are defined as any of the following: 1) Events that initiate the risk management protocol (i.e., expression of suicidal ideation or intent), 2) Events prompting an unscheduled emergency department visit not resulting in hospitalization, 3) Any unanticipated event that is unexpected and related to the study treatment. Serious Adverse Events (SAEs) are defined as outcomes resulting in death, hospitalization, life-threatening circumstances, person at risk of death at the time of the event, disability and/or incapacity, or events requiring intervention to prevent these outcomes. All hospitalizations are considered SAEs, with the exception of planned hospitalizations for elective procedures unrelated to the study intervention. AEs and SAEs are tracked through multiple surveillance mechanisms: spontaneous reporting by participants, discovery by study staff, identification by clinicians during therapy sessions, or detection during study assessments. When an AE is identified or reported, the therapist/data collector completes an Adverse Event Form immediately. This form documents the adverse event type, duration and timing, event details, and resolution status. AEs are reviewed periodically by a Data Safety Monitoring (DSM) team consisting of a physiatrist with extensive experience in msTBI research, and a statistician with expertise in clinical trials methodology. The DSM team also reviews and makes recommendations on recruitment, attrition, and other data relevant to the conduct of the trial and human subjects protections.

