For *Hypothesis 2a*, the primary endpoint is the change in average accelerometer activity counts/ day from post-intervention timepoint (T2 for IT participants, T2b for WL) to the follow-up endpoint, T3, 10 weeks later. The subject-specific T2/T2b-T3 changes will be modeled in an ANCOVA model as dependent on group (RB vs. No Tx) and the average accelerometer activity counts/day during the A phase (from timepoint T1 to post-intervention timepoint T2/T2b). The interaction between group and T1-T2(b) changes will be considered and retained in the model, if significant. If the interaction is not significant, Hypothesis 2a will be tested by comparing the mean change in RB vs. No Tx group using the model-based two-sided two-sample t-test with alpha 0.05. In the case of the main effects model (no significant interaction), this is equivalent to testing the main effect of RB (vs. No Tx) as the difference between intercepts of the regression lines with T1-T2(b) change as a predictor. A significant interaction would imply that the effect of RB (vs. No Tx) depends on the amount of change achieved during the A phase, and the test of interaction corresponds to comparing the slopes of the T1-T2(b) change regression lines between RB and No Tx groups. In the case of a significant interaction, the difference between RB and No Tx groups will be quantified in terms of the difference between the T1-T2(b) change regression slopes, and the significance (*p*-value) for that difference is the same as the significance (*p*-value) of the interaction. It is not expected that this interaction is important, and the study is not powered to detect such interaction. The secondary outcome measures (*Hypothesis 2b)* will be analyzed using the same approach.

We will report AEs and SAEs descriptively by treatment arm, including the number and percentage of participants experiencing at least one AE/SAE, as well as the total number of events by category. All AEs will be categorized by severity, relatedness to the intervention, and resolution status.

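### The adverse-event definition leaves out foreseeable, treatment-related harms that do not reach an emergency visit or SAE level, so related minor harms of increased activity would be undercounted

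*Protocol article*

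**What the plan says.** Section 2.4 (Procedure) defines an AE as any one of three things:

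1. an event that sets off the study's suicide-risk procedure;
2. an emergency department attendance that was not scheduled and did not end in admission;
3. "Any unanticipated event that is unexpected and related to the study treatment".

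SAEs are defined separately by outcome, with no test of expectedness. For example, "All hospitalizations are considered SAEs, with the exception of planned hospitalizations for elective procedures unrelated to the study intervention".

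The same section says "Adverse events (AEs) are documented systematically throughout the trial". The channels are spontaneous reports, discovery by staff, "identification by clinicians during therapy sessions", and the study assessments. Once an AE is identified, a form is completed with its type, timing and duration, details and resolution.

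Section 2.6 (Data analysis) states "We will report AEs and SAEs descriptively by treatment arm", as participants affected and event totals. AEs are then to be categorized by severity, relatedness and resolution. No AE rate, expected count or list of anticipated events is given.

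**The concern.** The intervention asks inactive people with moderate-to-severe brain injury to move more. Its plausible harms are mostly ordinary ones: falls, strains, flares of pain. These can be foreseen, and the article shows awareness of them. The Introduction lists pain, discomfort and safety among the known barriers to activity. Section 2.2 excludes people with contraindications to increased activity. Table 2 has the therapist direct participants toward safe activities.

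Under the third route, the more foreseeable a related harm is, the less likely it is to count. At stake is the trial's main statement about tolerability: a short AE table could look reassuring because the definition kept the relevant events out of it. An analysis plan cannot repair this later, because it cannot tabulate events that were never recorded.

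**Working it through.** **No plan figure to reproduce.** The article gives no safety rate or count. The efficacy power calculations do not depend on this point.

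**Step 1. Test an event against each route.** Take a related, foreseeable strain or fall during planned activity, with no emergency visit and no serious outcome.

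| Route (section 2.4) | Condition | Met? |
|---|---|---|
| AE 1 | Starts the suicide-risk procedure | No |
| AE 2 | Unscheduled emergency visit | No |
| AE 3 | Unexpected **and** related | No: related, but not unexpected |
| SAE | Serious outcome, or intervention needed to prevent one | No |

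The event is not an AE, and the AE form is completed only for AEs. If the same event led to an emergency visit it would count under route 2, whether expected or related or not. If it led to an unplanned hospital stay it would count as an SAE. The gap is limited to events below those two thresholds.

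**Step 2. Apply route 3 to the waitlist.** During T1–T2, WL participants have had no study treatment; section 2.1 says "WL participants then receive 10 weeks of GetUp&Go" only after that. An event in this period cannot be related to a treatment not yet given, so route 3 is empty for WL by construction. In T1–T2 the arms share only routes 1 and 2 and the SAE definition.

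**Step 3. Compare with the planned tabulation.** Section 2.6 plans to categorize AEs by relatedness and severity. For route 3 events relatedness is already a condition of entry, so that classification cannot separate them. The form content described in section 2.4 names neither severity nor relatedness. That may be condensation in the article, so it is not counted here as a contradiction.

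**Step 4. Illustrate the size.** Let *f* be the share of related harms that are foreseeable and *e* the share of those that reach an emergency department or hospital. Assume every unexpected related harm is recorded. Then

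share captured = (1 − f) + f × e.

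| f (assumed) | e = 0.05 | e = 0.10 | e = 0.20 |
|---|---|---|---|
| 0.5 | 0.525 | 0.55 | 0.60 |
| 0.7 | 0.335 | 0.37 | 0.44 |
| 0.9 | 0.145 | 0.19 | 0.28 |

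For example, with f = 0.9 and e = 0.05: 0.1 + 0.9 × 0.05 = 0.145. Across these ranges the definition captures between 60% and about 15% of related harms.

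**The case against.** **The gap is narrower than it may look.** Emergency visits and SAEs are counted regardless of expectedness, participants are medically screened, and pain interference is measured in all arms at each assessment. This stands as a limit on the point. However, a pain scale at scheduled assessments does not record falls or injuries, and screening does not change what counts as an event.

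**No list of anticipated events is given, so calling a fall expected is a judgement.** True. A given fall might be judged unexpected and recorded. But inclusion would then rest on case-by-case opinion about foreseeability, which is a weak basis for a harm count.

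**Stronger readings that the article does not support.**

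- *Unequal exposure.* A reader might infer that WL is compared over 10 + 10 + 10 = 30 weeks with IT over 10 + 10 = 20 weeks, a ratio of 1.5. That follows only if events are tabulated by original arm over the whole trial. Section 2.6 names no window and does not say which of the two randomizations defines the arm. Event timing is recorded, and within each randomized phase the comparison is 10 against 10 weeks. The table window is ordinary analysis-plan content.
- *Unequal detection.* A reader might set IT's five therapist sessions in T1–T2 (two in the first week, then weeks 3, 5 and 8) against none in WL. That counts one channel only. WL participants have periodic staff contacts, and spontaneous reports and assessments are open to both arms. The number of WL contacts is not given, so the size of any gap is unknown.
- *A biased arm comparison.* Longer follow-up would raise WL counts, while therapist contact and route 3 would raise IT counts. No net direction is shown. Reporting is descriptive, so no test or error rate is affected.

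**Conclusion.** The point holds for the scope of the AE definition. As written, the rule lets foreseeable, related, non-serious harms below the emergency-visit threshold go unrecorded, and route 3 cannot be met in WL before treatment. The descriptive summary would therefore undercount related minor harms. This follows from the stated definition and needs no assumption about rates.

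The size does need assumptions. The range of 60% down to about 15% captured rests on assumed shares of foreseeable harms (50–90%) and of those reaching emergency or hospital care (5–20%), because the article supplies neither. It illustrates the size and is not an estimate for this trial. The efficacy analyses, the power statements and the capture of serious events are unaffected. The documents do not establish a biased comparison between IT and WL.

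**What to change.** Amend section 2.4:

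- Remove the unexpectedness condition from the third route.
- Record untoward events linked to physical activity (falls, musculoskeletal injuries and similar) in every arm, whether or not expected. This includes WL before treatment.
- Put expectedness, severity and relatedness on the AE form as later classifications. Section 2.6 already plans to report severity and relatedness.

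Preferably, ask the same scripted question in existing contacts in both arms, by unmasked staff or as the last item of the call. The current script asks participants not to discuss their program experiences with data collectors, so placement matters. Placing it last does not fully protect later calls made by the same assessor; using unmasked staff avoids this.

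It would also help to state that AE tables follow the randomized phases: IT versus WL over T1–T2, and RB versus No Tx over follow-through. This removes any doubt about unequal observation time.

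The cost is a short amendment, one extra question and more minor events to log. Recruitment began in December 2023 and is expected to run to December 2026, so earlier and later participants will have different ascertainment. Flag events by whether they fall before or after the change and report the two periods separately.

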### Intervention

2.5

The overall goal of the intervention is to develop and support a personalized plan to increase physical activity and decrease sedentary behavior, using treatment ingredients consonant with the COM-B model (27). The ingredients in each COM-B domain (Capability, Opportunity, Motivation) that are supplied by the therapist and by RehaBot are summarized in Table 2.

**Table 2 T2:** Treatment ingredients in theoretically defined domains in the GetUp&Go program. Ingredients delivered via RehaBot are *italicized.*

COM-B domain	Treatment Ingredients
Capability: Physical	-Elicit past skills/ experiences and current preferences re: PA -Steer P toward safe/ appropriate activities as per MD/ PT screening; provide instruction for safe/ effective PA as needed
Capability: Psychological/ Cognitive	-Education about PA: benefits, types, dose-response relationship -Provide menus and ideas for PA at all levels of intensity; indoors and outdoors; scheduled bouts and incidental activity -Teach how to monitor exertion level, as needed -Provide structure and prompts for action planning (where, when, how, how often, with whom PA will be performed) and coping planning (how to deal with anticipated obstacles to PA) -*Provide reminders of planned activities in P's daily environment* -*Provide on-demand support by reminding P of daily plans and coping plans*
Opportunity: Social	-Elicit information about familial and sociocultural norms/ factors that may affect P's pursuit of PA -Encourage P to solicit support and/ or co-participation in PA from family and friends
Opportunity: Physical	-Assess/ discuss perceived neighborhood characteristics (walkability, aesthetics, safety, amenities) -Assess/ discuss home/ lifestyle affordances (space, time); assist with time management as needed -Elicit information, problem-solve, and provide tips regarding equipment/ clothing, facilities, transportation, costs, other resources -Encourage PA in varied contexts to promote generalization
Motivation: Reflective	-Assist P in formulating/ stating macro goals and intentions regarding PA; prompt/ discuss self-assessment of commitment level -Assess self-efficacy regarding chosen PA, ability to cope with obstacles, and ability to schedule PA in daily life; provide feedback and information to enhance self-efficacy; remind P of past and current successes -Assess for, encourage, and reinforce autonomous motivation for PA -Elicit expected positive outcomes; elicit and educate re: negative beliefs -Teach/ encourage motivational self-talk, including implementation intentions -Provide verbal reinforcement and feedback on gains -*Support self-monitoring by prompting P to report on progress towards goals and positive outcomes/ satisfaction with increased PA in their daily environment as they complete activities* -*Provide reinforcing messages in the moment as P completes activities* -*Provide on-demand feedback on accomplishments and progress towards goals* -*Provide on-demand support by reminding P of macro goal intentions regarding PA*
Motivation: Automatic	-Explore P's implicit associations with PA as pleasant/ unpleasant -Steer P toward activities that evoke pleasure, enjoyment -Explore and encourage P's values related to PA and self-identification as an (e.g.) active person/ fit person/ role model to others -Prompt P to use habit formation strategies such as distinctive activity-initiation cues in environment, time-of-day cues -*Assist in habit formation by cuing P's activities in daily environment*

P, participant; MD, medical doctor; PT, Physical Therapist; PA, physical activity.

The 10-week GetUp&Go intervention is delivered entirely remotely. The first 2 sessions last 60–90 min each and are delivered within the first week over Zoom for Healthcare (or smartphone if needed). The following 3 sessions (in weeks 3, 5, and 8) are delivered by phone and last 30–45 min. The RehaBot app is installed on the participant's phone in Session 2 followed by a guided overview and brief training that includes hands-on practice, troubleshooting, and opportunities to ask questions, until the participant expresses confidence in using the app. Participants who do not own a smartphone or do not have access to a computer/ tablet are issued a phone with unlimited texting and/ or an iPad for the duration of the trial. To maximize scheduling flexibility, participants are assigned to one of 4 therapists: Two doctoral level neuropsychologists, one Masters-trained clinician with extensive experience in neuropsychological approaches to the treatment of msTBI, and one doctoral-level Physical Therapist. All therapists are experienced clinicians with specific expertise in treating persons with msTBI. To ensure fidelity, a detailed manual is used for all treatment sessions. In addition, two therapists were present during treatment sessions for the first four participants in the trial in order to achieve proficiency and consistency in delivering the intervention. All therapists continue to meet weekly to review cases to ensure that their approaches and procedures are comparable.

In Session 1, the therapist provides education on the benefits of PA, emphasizing the dose-response relationship (i.e., the fact that *any* degree of PA increase is potentially beneficial). In discussion with the participant, the therapist explores in more depth the factors revealed in screening, and they begin to brainstorm a list of possible activities and routines to increase PA/ decrease sedentary behavior within the participant's preferences and opportunities in the home and community environment. The therapist promotes consideration of new activities, existing activities that might be modified or increased, and ways to “sneak in” PA, such as taking extra steps to reach a destination. The therapist also elicits overall goals and specific intentions regarding increased PA and reduction of sedentary time (64, 76), expected outcomes (64), and other statements for later use as personalized motivational reminders, delivered by RehaBot. The capabilities of RehaBot are explained and demonstrated in Session 1 using sample screen shots, to help participants begin to consider how they might benefit from using the app. See Figure 2 for sample screenshots.

**Figure 2 F2:**
[figure not shown]
Example of RehaBot screens during interaction with participant.

As the list of planned activities takes shape, the therapist engages the participant in action planning, i.e., specific plans for when, where, how often, and (if applicable) with whom activities will occur during the week (64, 76–78). Additional discussion involves potential barriers to activity completion, and possible ways of overcoming them. Obstacles may be overcome with various types of coping plans for one-time solutions (e.g., buying suitable shoes for walking or jogging; joining the nearby fitness center), or via just-in-time reminders framed as implementation intentions (76, 79, 80) (e.g., “If I don't feel like taking my walk, I’ll remind myself that….”) that may be accessed through RehaBot.

In Session 2, RehaBot is installed on the participant's phone, the participant is trained on all of its features, and the therapist and participant collaborate on personalizing the app. RehaBot is accessed via regular text-messaging, and engages in bi-directional communication with the user (see Figure 2). Therapists use a portal to enter participants' action plans, coping plans, goals, and other relevant data into the RehaBot app. Message timing is fully customizable. Participants select their preferred times for daily “good morning” and “good evening” check-in messages. They also determine how many activity reminder messages they wish to receive throughout the day and when those reminders should be delivered. Scheduled contacts come in the form of text message reminders to check your plan for the day, carry out a planned activity at a scheduled time, and report on your accomplishments. However, RehaBot is also available on-demand to serve as a “coach” to provide reminders, suggestions, feedback, reinforcement, coping plans, and personalized motivational messages. Activity reminder messages are worded using the participant's own language and selected activities. Participants also personalize the content of activity suggestions and the language and content of their coping plans. When an activity is logged as complete, RehaBot sends encouraging messages that reinforce the effort and tie the participant's accomplishments to progress towards a specific personal goal. Self-efficacy, thought to be a strong mediator of positive behavior change, is a particular target of intervention via specific positive feedback from both therapist and chatbot, and reminders of task mastery and overall progress (81).

In the phone sessions in weeks 3, 5, and 8, the participant's plan and their reactions to it are reviewed. Progress is reinforced, problems and obstacles are addressed, and any desired changes to the plan are instituted in the RehaBot portal. In the final telephone session, the therapist guides the participant in reflecting on their overall progress and their ability to overcome barriers to physical activity, while offering feedback on positive changes observed throughout the intervention. The participant continues to use RehaBot independently until Week 10, when they receive a letter reminding them of the upcoming telephone data collection and Actigraph wear period.

Participants randomized to RB for the FT phase receive a call notifying them that their RehaBot plan will remain in place for another 10 weeks. These participants are encouraged to use RehaBot to continue with their activity plans until the next evaluation period. Those randomized to No Tx are reminded of the final evaluation in 10 weeks and encouraged to keep up their PA plans. Neither FT condition includes any further contact from the therapist, although we would respond to participants who contacted us regarding a technical problem with the app.

### Data analysis

2.6

For the primary endpoint (*Hypothesis 1a*: **primary hypothesis**) and each of the secondary endpoints (*Hypothesis 1b*), the mean change from T1 to T2 in the IT group will be compared to the mean change from T1 to T2 in the WL group using the two-sided two-sample t-test with alpha = 0.05. The mean change in each group and the mean difference between changes in IT vs. WL group will be estimated with the corresponding 95% confidence interval. If the normal distribution assumption is not appropriate for patient-specific changes in one or both groups, then the two-sided two-sample Wilcoxon test will be used instead of the t-test. We will employ intent-to-treat for the *primary analysis*, and as such, we will make every attempt to collect T2 outcome data on all randomized participants regardless of treatment received. Per current recommendations (82–84), we will use multiple imputation to account for missing T2 data, and evaluate missingness assumptions (by comparing available data for participants with complete vs. missing T2). If the assumption of the data being *missing at random* is not appropriate, the imputations will be performed using the methods specifically developed for data *missing not at random* (85). As a *secondary analysis* we will perform a complete-case analysis with dropouts excluded. With the proposed sample size of 35 subjects per arm and assuming up to 15% loss to follow-up, we expect to have at least 30 subjects per arm available for analysis. The sample size of 30 subjects per arm provides 81% power to detect the mean difference between changes in IT vs. WL arms corresponding to the effect size of 0.75 (effect size for the primary endpoint as reported in Clanchy et al. (24) using the two-sided two-sample t-test with alpha 0.05.

For *Hypothesis 2a*, the primary endpoint is the change in average accelerometer activity counts/ day from post-intervention timepoint (T2 for IT participants, T2b for WL) to the follow-up endpoint, T3, 10 weeks later. The subject-specific T2/T2b-T3 changes will be modeled in an ANCOVA model as dependent on group (RB vs. No Tx) and the average accelerometer activity counts/day during the A phase (from timepoint T1 to post-intervention timepoint T2/T2b). The interaction between group and T1-T2(b) changes will be considered and retained in the model, if significant. If the interaction is not significant, Hypothesis 2a will be tested by comparing the mean change in RB vs. No Tx group using the model-based two-sided two-sample t-test with alpha 0.05. In the case of the main effects model (no significant interaction), this is equivalent to testing the main effect of RB (vs. No Tx) as the difference between intercepts of the regression lines with T1-T2(b) change as a predictor. A significant interaction would imply that the effect of RB (vs. No Tx) depends on the amount of change achieved during the A phase, and the test of interaction corresponds to comparing the slopes of the T1-T2(b) change regression lines between RB and No Tx groups. In the case of a significant interaction, the difference between RB and No Tx groups will be quantified in terms of the difference between the T1-T2(b) change regression slopes, and the significance (*p*-value) for that difference is the same as the significance (*p*-value) of the interaction. It is not expected that this interaction is important, and the study is not powered to detect such interaction. The secondary outcome measures (*Hypothesis 2b)* will be analyzed using the same approach.

We will report AEs and SAEs descriptively by treatment arm, including the number and percentage of participants experiencing at least one AE/SAE, as well as the total number of events by category. All AEs will be categorized by severity, relatedness to the intervention, and resolution status.

With regard to power, in the study of Clanchy et al. (24), participants in the active intervention group lost a mean of 1.7 standard deviations in average activity counts per day between their post-treatment and follow-up assessments, without any treatment during this time (comparable to our No Tx condition). We hypothesize that the loss in activity in the RB (treated) group in our study will be reduced by at least 50% of this value, an expected difference in effect size between RB and No Tx groups of 0.85. We make the conservative assumption of up to 15% additional attrition during the FT phase, leaving *N* = 46. With this sample size we will have 80% power to detect a difference in effect size of at least.85 between groups, using the two-sided two-sample t-test with alpha 0.05.

The analyses of predictors of treatment response will be exploratory, as the large number of predictors of possible interest will preclude hypothesis-driven methods. We will consider the use of analysis techniques such as model averaging (86, 87)*,* a method that allows for more robust conclusions about important candidate predictors when the possible predictors are numerous and the sample is relatively small, and when different variable selection methods may result in different and possibly suboptimal models.

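### The unadjusted change-score t-test for H1a and H1b is valid but less precise than adjusting for T1, and the Wilcoxon fallback would not test the mean difference that is reported

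*Protocol article*

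**What the plan says.** Section 2.6 (Data analysis) of the protocol article gives one rule for the primary endpoint (H1a) and every secondary endpoint of the first phase (H1b). The IT mean change is compared with "the mean change from T1 to T2 in the WL group using the two-sided two-sample t-test with alpha = 0.05". No covariate enters the test.

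The same paragraph makes the test conditional on the data: "If the normal distribution assumption is not appropriate for patient-specific changes in one or both groups, then the two-sided two-sample Wilcoxon test will be used" in place of the t-test. The quantity to be reported is stated before that condition and does not change with it: "the mean difference between changes in IT vs. WL group will be estimated with the corresponding 95% confidence interval". The analysis is by intention to treat, with multiple imputation of missing T2 values.

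On power: "The sample size of 30 subjects per arm provides 81% power to detect the mean difference between changes in IT vs. WL arms". The standardized effect behind that figure is 0.75, taken from an earlier trial.

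Section 2.4 (Procedure) requires all baseline data, accelerometer data included, to be in hand before randomization. A T1 value should therefore exist for everyone randomized.

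**The concern.** There are two separate issues.

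**Precision.** A change score uses the baseline, but with its slope fixed at 1. When the true slope is below 1, which is usual for a noisy repeated measurement, subtracting the whole baseline adds variance that a regression on T1 would remove. In a trial of 70 people planned at 81% power, that variance matters and can be removed without cost.

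**Test and estimate.** The t-test and the mean difference with its interval answer the same question. The Wilcoxon test compares ranks. If it supplies the p-value while the mean difference supplies the estimate, the two can disagree, and the article does not say which carries the conclusion. The usual combining rules for multiple imputation need an estimate and a variance from each completed dataset. A Wilcoxon p-value is neither.

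**Working it through.** **Inputs from section 2.6:** 35 randomized per arm, up to 15% loss (35 × 0.85 = 29.75, about 30 analysed), effect size 0.75, two-sided alpha 0.05. The effect size is read here as SD units of the change score.

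**Inputs assumed:** the T1–T2 correlation ρ, which the article does not give, so a range of 0.4 to 0.9 is shown; and equal variance σ² at T1 and T2.

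**Step 1, the plan's own figure.** Noncentrality = 0.75 × √(30/2) = 2.905 with 58 degrees of freedom. The noncentral t distribution gives power of 81.5%, so the stated 81% reproduces.

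**Step 2, variance under each analysis.**
- Change score: variance 2σ²(1 − ρ).
- ANCOVA on T1: residual variance σ²(1 − ρ²).
- Ratio, ANCOVA to change score: (1 + ρ)/2.

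**Step 3, power of ANCOVA for the same raw difference.** Effective d = 0.75/√((1 + ρ)/2), with 57 degrees of freedom to charge for the covariate. The last column is 30 × (1 + ρ)/2, the number per arm that would match the precision of 30 per arm on change scores.

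| ρ | Variance ratio | Effective d | Power | Equivalent n per arm |
|---|---|---|---|---|
| 0.4 | 0.70 | 0.896 | 92.7% | 21.0 |
| 0.5 | 0.75 | 0.866 | 90.9% | 22.5 |
| 0.6 | 0.80 | 0.839 | 89.1% | 24.0 |
| 0.7 | 0.85 | 0.813 | 87.2% | 25.5 |
| 0.8 | 0.90 | 0.791 | 85.3% | 27.0 |
| 0.9 | 0.95 | 0.769 | 83.4% | 28.5 |

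**Step 4, if the variances differ.** Let k be the ratio of the T2 SD to the T1 SD. The change-score variance minus the ANCOVA residual variance is σ₁²[(1 + k² − 2kρ) − k²(1 − ρ²)] = σ₁²(1 − kρ)². This is never negative, and it is zero only when the slope kρ equals 1. The direction of the gain does not depend on equal variances; its size does.

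**Step 5, the switch.** The article gives no numerical trigger, so the check assumed Shapiro–Wilk p < 0.05 in either arm. It simulated 30 per arm, with 20,000 runs for each null case.
- Same shape in both arms (normal, t with 4 df, lognormal, exponential): the two-stage rule rejects a true null in 4.7% to 5.0% of runs. It switches in about 10% of runs with normal data and in almost all with exponential data.
- Equal means but different shapes (normal against exponential): the t-test rejects in 5.1% of runs, and the Wilcoxon test and the two-stage rule each in 8.1%.

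The second case illustrates the mismatch: with no difference in means, the Wilcoxon test rejects more often than 5% because it is answering a different question.

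**The case against.** The change-score t-test is unbiased under 1:1 randomization, fits H1a as worded (a greater increase from baseline) and has the power claimed for it. All of that stands. A reader might infer that the primary analysis is invalid, that 81% is wrong or that the baseline is thrown away; the article supports none of these.

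The size of the gain rests on a correlation the article does not give. This stands too: at ρ = 0.9 the gain is about 2 points.

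Chance baseline imbalance might look like a further harm. With 35 per arm, a one-standard-error imbalance is √(2/35) = 0.239 SD. At ρ = 0.6 it moves the change-score estimate by 0.4 × 0.239/√0.8 = 0.107 change-score SD, or 14% of 0.75. But it can go either way, adds no bias under randomization, and is already counted in the variance comparison.

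It is also tempting to call the plan inconsistent because H2a is analysed by ANCOVA. That model adjusts for what happened in the preceding treatment phase, because H2a itself asks for that adjustment. H1a has no such clause, so there is no contradiction.

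On the switch, one might infer an inflated error rate. Step 5 does not show that for a fixed rule with equal-shaped arms, and the 8.1% belongs to a constructed case. Choosing whichever p-value is smaller would inflate the error, but the article does not allow it: the trigger is the normality assumption. The exact criterion may sit in an analysis plan not shown and is not held against the article. The fallback also has a real benefit: in the simulated skewed or heavy-tailed cases with a pure shift of 0.75 SD, the Wilcoxon test had 91% to 96% power against 82% to 84% for the t-test. Approximate ways to combine rank statistics over imputations can be devised. None of this makes the Wilcoxon p-value a test of the mean difference that the article commits to reporting.

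**Conclusion.** The point holds as an improvement that should be made, not as an error that invalidates the trial.

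- **Precision.** Adjusting for T1 cuts the variance by 5% to 30% over ρ = 0.9 to 0.4 and raises power from 81.5% to between 83.4% and 92.7%. This assumes equal T1 and T2 variances and 0.75 in change-score SD units. Confidence is high in the direction and limited in the size.
- **Test and estimate.** If the fallback is triggered, the p-value and the mean difference with its interval will address different questions, and the p-value does not combine directly over the imputed datasets. This is conditional on non-normality and is no evidence of general type I error inflation.

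**What to change.** Before any arm-level analysis, name one primary analysis for H1a and for each H1b endpoint: ANCOVA of the T2 value on arm and the T1 value, fitted within each imputed dataset and pooled. Take the adjusted mean difference, 95% confidence interval and p-value all from that model. Using change instead of T2 as the outcome, with T1 still in the model, gives the same arm coefficient, so the hypothesis as worded is still the one tested.

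If skew is expected, settle now on robust standard errors or a fixed transformation. Keep the change-score t-test and the Wilcoxon test as sensitivity analyses that never replace the primary result.

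The cost is a change of wording. No new data or participants are needed, and section 2.4 expects recruitment to run until December 2026, which should leave time.
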